### Participants

#### Inclusion criteria

The following are the inclusion criteria: (1) 18–75 years old; (2) primary gastric adenocarcinoma (papillary, tubular, mucinous, signet ring, undifferentiated adenocarcinoma) confirmed pathologically by endoscopic biopsy before surgery; (3) cT1-4a, cNany, cM0 according to the AJCC classification (version 7.0) before surgery; (4) absence of adjacent organ invasion and distant metastasis; (5) ECGO score 0 or 1 and ASA grades I–III; (6) signed informed consent.

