### Sample size

This study is a superiority testing trial (one-tailed trial) of which the primary outcome is the number of retrieved LNs and study subjects will be divided into 4 groups. Combined with our previous findings and literature reports, the standard deviation σ of the total number of LNs in control group was 8.6 [9, 13, 17]. The *α* (test level) is set as 0.05 and power (1-β) is 0.8. A difference of more than 3 in the total number of detected LNs will be considered as significant, i.e., the effect value *d* = 3/*σ* = 0.35. Thus, at least 103 (102.3) participants are required in each group. Considering an expected dropout rate of 20%, 129 (128.75) participants are finally required in each group, leading to a total of 516 participants.

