### Randomization

Participants will be randomized into dual tracer, ICG, CNs, or control (non-tracing) group. A random digit table is used for randomization as follows: (1) according to the order of inclusion, each participant will be allocated a random number, and (2) divide the number by 4. If the remainder is 0, the participant will be enrolled into dual tracing group. If the remainder is 1, the participant will be enrolled into non-tracing group. If the remainder is 2, the participant will be enrolled into CNs group. If the remainder is 3, the participant will be enrolled into ICG group. The allocation is not blinded to surgeons or participants before performing procedure.

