#### Intraoperative lymph node localization and dissection

After anesthesia, ICG (Dandong Yichuang Pharmaceutical Co., Ltd.) powder is diluted into 2.5 mg/ml with saline and then injected into subserosal layer using “hexa-site” method in the ICG group and dual tracer group [18]. Briefly, the injection is performed at 3 sites along the lesser curvature (first branch of left gastric artery, angular and first branch of right gastric artery). Similar injection was repeated along the greater curvature.

A near-infrared (NIR) fluorescence imaging system (PINPOINT, NOVADAQ, Mississauga, ON, Canada) is used to obtain near-infrared fluorescence imaging during surgery. It provides high-definition white light visual field, near-infrared fluorescence visual field, and ICG-specific SPY visual field as well as merged visual field. LN dissection in the ICG group and dual tracer group is performed under the fluorescent laparoscope.

The standard sequence of LN dissection is as follows: (1) total gastrectomy: No. 6 → No. 7, 9, 11p → No. 8a, 12a, 5 → No.1 → No. 4sb → No. 4sa, 11d → No.2; (2) distal subtotal gastrectomy: No. 6 → No. 7, 9, 11p → No. 3, 1 → No. 8a, 12a, 5 → No. 4sb. Selective dissection of No.10 LNs is performed when (1) the primary tumor is located in the middle/upper stomach and invaded a large extent, (2) preoperative radiology suggests splenic lymphadenopathy, (3) significant fluorescent signal of No. 10 LNs, and (4) black stained No. 10 LNs by CNs. Surgical area is routinely inspected for possible residual fluorescent LNs or black-stained LNs, and additional dissection will be performed if necessary. D2 + LN dissection will be performed if fluorescent or black-stained LNs (such as No. 10 or No. 14v) are observed outside D2 region.

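### Eligibility names no planned resection while the dissection sequence covers two operations only, so the extent of resection may be settled after the surgeon knows the arm

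*Protocol article*

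**What the plan says.** **Eligibility.** The Inclusion criteria define the disease by histology and by stage: "cT1-4a, cNany, cM0 according to the AJCC classification (version 7.0) before surgery". Neither they nor the Exclusion criteria mention tumour site or intended resection. Middle and upper tumours are expected, because the Intervention section makes No. 10 dissection depend partly on them.

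**Dissection.** The section on intraoperative localization and dissection gives a standard sequence for total gastrectomy and a second one: "2) distal subtotal gastrectomy: No. 6 → No. 7, 9, 11p → No. 3, 1 → No. 8a, 12a, 5 → No. 4sb". No other resection is listed.

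**Allocation.** Randomization uses the remainder of a random number divided by 4, with no stratification described. The section adds: "The allocation is not blinded to surgeons or participants before performing procedure". Surgery may follow enrolment by up to 14 days, and carbon nanoparticles are injected the day before in two of the four arms.

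**Recording and analysis.** Procedure type and tumour location appear under Surgical parameters, within the intraoperative data. The primary outcome is the total number of retrieved LNs, and Data analysis names a t test for quantitative data.

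**The concern.** The total LN count depends on how much stomach is removed and which stations go with it, as well as on how well nodes are seen. If the choice between a larger and a smaller resection is still open when the surgeon learns the arm, the mix of operations can differ between arms for reasons other than tracing, and the t test takes no account of it.

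This cannot be mended afterwards by adjusting for the operation performed. That variable arises after allocation. If the arm influenced it, patients with the same operation in different arms are no longer comparable, and part of any real effect may be adjusted away. Only a plan fixed before allocation is a valid baseline covariate.

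Separately, the status of a patient planned for a resection outside the two listed is unclear. The eligibility lists do not exclude that patient and no sequence applies. The Withdrawal criteria include treatment that departs from the protocol, but do not say whether an unlisted operation counts.

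**Working it through.** **1. The plan's own figure.** The Sample size section gives a one-tailed test, alpha 0.05, power 0.8, a difference of 3 nodes and an SD of 8.6 ("of the total number of LNs in control group was 8.6").
- Normal formula: 2 × ((1.645 + 0.842) / (3/8.6))² = 101.6 per group. The t-distribution version gives 102.30, matching the stated 102.3, so 103.
- Dropout: 103/0.8 = 128.75, so 129; 4 × 129 = 516.
- Power at 103 per group: 0.805 (normal approximation).

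The sample size reproduces and is not in dispute.

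**2. The two sequences side by side.**
- Both lists: 1, 4sb, 5, 6, 7, 8a, 9, 11p, 12a (9 stations).
- Total gastrectomy only: 2, 4sa, 11d (3 more, 12 in all).
- Distal subtotal only: 3 (1 more, 10 in all).

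The lists differ, but they state an order of work. No. 3 is absent from the larger operation's list, so they are weak evidence of the exact station sets.

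**3. Illustration of a shift.** The document gives no LN counts or case shares by resection, so both inputs here are assumptions: D, the mean LN gap between larger and smaller operation (5 to 10), and s, the between-arm difference in the share of the larger operation (10 points).
- Shift = D × s = 5 × 0.10 to 10 × 0.10 = 0.5 to 1.0 nodes, or 17% to 33% of 3.
- Standard error of a two-arm contrast: 8.6 × √(2/103) = 1.198.
- With no tracer effect and a systematic shift favouring the tracer arm, one-sided rejection = 1 − Φ(1.645 − shift/1.198) = 0.11 to 0.21, instead of 0.05.
- With a true 3-node effect and the shift against the tracer arm, power = Φ((3 − shift)/1.198 − 1.645) = 0.67 to 0.51.

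Over a wider range (D from 3 to 10, s from 5 to 20 points) the shift runs from 0.15 to 2.0 nodes.

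**4. Chance imbalance.** Under simple randomization, with 30% to 50% total gastrectomies assumed, the SD of the between-arm difference in share is √(2p(1 − p)/103) = 6.4 to 7.0 points. A 10-point difference is thus about 1.4 to 1.6 SDs (10/7.0 to 10/6.4) and could arise by chance alone. The t test already allows for chance imbalance; it does not allow for a shift caused by knowledge of the arm. Without a record made before allocation, the two cannot be told apart.

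**The case against.** **Silence of a condensed article.** The full protocol is not shown, and a list of permitted operations or a planned-procedure field could be in it. This stands in part: the missing pre-allocation record is an inference from silence. The mismatch between the eligibility lists and the dissection section, and the open allocation, are stated text.

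**The operations are not unrestricted.** A reader might infer that any resection is admitted and that, for example, proximal gastrectomy patients will enter without a protocol dissection. The document does not support this. All arms have laparoscopic radical gastrectomy, conversion and most combined surgery are exclusions, certain incomplete D2 or R0 resections lead to withdrawal, and the two sequences may well be meant as the two trial operations. Proximal gastrectomy is never mentioned. What remains is that the article does not say so.

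**No sign of steering.** Nothing suggests that surgeons would choose the resection by arm. They need at least 100 procedures, each operation is filmed in full, and procedure type is recorded, so a large imbalance would be visible. This is fair, but seeing an imbalance in performed operations does not show whether it was planned before allocation.

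**Part of the strategy.** The Discussion expects the dual tracer to improve tumour localization, so a changed resection could be a genuine consequence of tracing. Extra dissection prompted by a tracer signal certainly belongs to the intervention and is not criticised here. This affects interpretation, and it is a further reason to show changes from plan by arm.

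**Conclusion.** The point holds as a design weakness; no figure in the plan is wrong. The eligibility and dissection sections need reconciling, and a determinant of the primary outcome may be settled after the arm is known, with no baseline record described against which to check it.

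The size cannot be derived from the document. The 0.5 to 1.0 node shift rests on an assumed 5 to 10 node gap and an assumed 10-point difference in share. The rejection and power figures further assume that the whole difference is systematic.

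Two stronger readings should be set aside:
- That choice of procedure could by itself create or hide the 3-node target. This would need D × s = 3, that is a 30-point difference in share with a 10-node gap or 60 points with a 5-node gap. Nothing in the document points to that.
- That unlisted resections would lower power by a known amount. Any such figure assumes that the SD of 8.6 excludes spread between procedures. The Sample size section takes it from the centre's own findings and literature without a breakdown by procedure, so the spread may already be included.

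**What to change.** 1. State in the eligibility criteria whether resections other than total and distal subtotal gastrectomy are eligible, and align the dissection section and the Withdrawal criteria with that statement. Which operations to admit is the sponsor's decision.
2. Enter the planned resection and the tumour location in the CRF before the random number is drawn.
3. Compare LN counts with the planned resection as a baseline covariate instead of by an unadjusted t test. Do not adjust for the resection performed.
4. Report changes from planned to performed resection by arm, with reasons.

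The record does not prevent a change after allocation, and the covariate deals only with baseline differences. Together with step 4, the record makes any change visible, which cannot be reconstructed reliably once the arm is known.

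The cost is one added CRF entry and a small change to the model. If the sponsor limits eligibility to the two listed operations, a few patients are lost.

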#### Exclusion criteria

The following are the exclusion criteria:(1) pregnant or lactating women. (2) serious mental disease; (3) previous upper abdominal surgery (except laparoscopic cholecystectomy); (4) previous gastric surgery (including ESD and EMR); (5) refusal to laparoscopic surgery; (6) allergy to iodinated contrast agents; (7) peri-gastric LN larger than 3 cm in preoperative imaging; (8) history of other malignancies within recent 5 years; (9) preoperative neoadjuvant chemoradiotherapy; (10) unstable angina pectoris or myocardial infarction within recent 6 months; (11) continuous systemic use of hormones within recent 1 month; (12) combined with other surgeries (except appendectomy or cholecystectomy); (13) emergent surgery due to complications caused by gastric cancer (bleeding, perforation or obstruction); (14) FEV1 less than 50% of the predicted value; (15) conversion to laparotomy.

#### Withdrawal criteria

The following are the withdrawal criteria: (1) diagnosis of M1 during or after surgery, i.e., distant metastasis upon intraoperative exploration or postoperative pathology, or positive exfoliated cells in the abdominal cavity; (2) duodenum invasion of diagnosis of T4b during or after surgery; (3) incomplete D2 dissection or R0 resection owing to masses formed by regional LNs coalescing or vital vessel surrounding; (4) necessary additional surgery during operation; (5) serious perioperative complications (unable to tolerate surgery or anesthesia); (6) referring to emergent surgery due to condition changes judged by attending physicians; (7) voluntary withdrawal or discontinued treatment due to personal reasons at any stage; (8) treatment violates study protocol.

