#### Intraoperative data collection

##### Video data

Intraoperative LN dissection and postoperative specimen profile will be photographed and archived for each participant. Furthermore, the entire laparoscopic procedure will be videotaped, and the unclipped files will be saved for evaluation. All photos and videos will be stored in hard drivers for a minimum of 3 years. The procedure will be judged as disqualified if photographs or videos are incomplete.

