### Data analysis

Database will be established using Epidata 3.0, and statistical analysis will be performed using SPSS 18.0. This trial uses differential testing; a *p*-value less than 0.05 will be considered statistically significant, and the confidence intervals for the parameters will be estimated as 95%.

In this trial, validity analysis based on MITT (modified intention to treat) analysis will be conducted. The primary and secondary outcomes will be analyzed with both MITT and PP (per protocol) analysis. Conclusion of MITT analysis will be the primary analytical method, and if the conclusions of PP analysis and MITT analysis are consistent, the credibility of the conclusions can be improved. SP (safety population) analysis will be used to analyze laboratory evaluations, adverse events, and adverse reaction data. SP will be defined as the denominator for the incidence of adverse reactions.

Descriptive statistics will be used to systematically describe primary and secondary outcomes. Means, standard deviations, and confidence intervals will be presented based on data from the control group and intervention groups. Frequency distributions, percentages, medians, and mean rank order will be presented based on quantitative data and rank data. Positive rates, positive number, and total number of retrieved LNs will be presented based on qualitative data. The number of events, number of missingness, median survival time, and survival rate will be presented based on survival data. Efficacy analysis will be performed on data following descriptive statistics. This study utilizes Pearson chi-square test for qualitative data, *t* test for quantitative data, Wilcoxon rank sum test for ranked data, Log-rank test for univariate analysis and Cox regression model for multivariate analysis of survival data, and two-tailed test for safety indicators and incidence of adverse reactions.

Abnormal values will be judged when the observed value is greater than P75 or less than P25, and 3 times more than the interquartile range defined as P75 subtracts P25. Sensitivity analysis will be performed on the abnormal data, and the data will be retained if results are not contradictory. If there is a contradiction, specific analysis will be conducted.

Subgroup analysis will be performed to identify risk factors for the prognosis according to the specific circumstances of the data.

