#### Interim analysis

Safety interim analysis and futility interim analysis will be conducted every 8 months, and analysis report will be submitted to the Efficacy and Safety Evaluation Committee. The specific contents of the report include the following: ineligible patients/potentially ineligible patients, reasons for end of treatment/discontinuation/study protocol, adverse events and serious adverse events, completion rate of laparoscopic surgery, proportion of conversion to laparotomy, enrolled protocol deviations, disease-free rate/disease-overall survival rate of all participants, etc. The Efficacy and Safety Evaluation Committee will review and discuss the report in accordance with the procedures documented in the Clinical Safety Information Management Guidelines and make written recommendations to the study director including whether to continue the enrollment of the study.

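### Conversion to laparotomy is an eligibility exclusion and other intraoperative events are withdrawal criteria, and nothing keeps these patients in the primary MITT set

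*Protocol article*

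**What the plan says.** All places are in the Protocol article, Methods.

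- **Timing and blinding.** Under Randomization, allocation follows the order of inclusion and is open to surgeons and participants before the procedure. Under Preoperative administration of CNs, surgery follows within 2 weeks of enrolment, and CNs are injected the day before surgery in two of the four arms. Allocation therefore precedes the operation.
- **Exclusion criteria.** The last item is "15) conversion to laparotomy". Surgical parameters also lists conversion and its reason as data to record, and Interim analysis reports the "proportion of conversion to laparotomy".
- **Withdrawal criteria.** These include "1) diagnosis of M1 during or after surgery, i.e., distant metastasis upon intraoperative exploration or postoperative pathology", "3) incomplete D2 dissection or R0 resection owing to masses formed by regional LNs coalescing or vital vessel surrounding", additional surgery found necessary during the operation, "5) serious perioperative complications (unable to tolerate surgery or anesthesia") and "8) treatment violates study protocol".
- **Date management.** Missing values are not imputed, and participants who have them are withdrawn from the study.
- **Video data.** "The procedure will be judged as disqualified if photographs or videos are incomplete".
- **Data analysis.** "Conclusion of MITT analysis will be the primary analytical method". PP is the check on it, and agreement between the two is said to raise credibility. The article does not say which patients form either set.
- **Sample size.** 103 per group is raised to 129 for an expected 20% dropout.

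**The concern.** Conversion happens during the operation, so it cannot screen patients at entry. The protocol uses it both as an eligibility rule and as a result. The withdrawal criteria likewise turn on what is found or done at or after surgery.

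The arms need not meet these criteria equally often. Under Intraoperative lymph node localization and dissection, stained nodes can trigger No. 10 dissection or an extension beyond D2, which cannot occur in the control arm. More extensive surgery could plausibly change rates of conversion, additional surgery or deviation. The surgeons who make these judgements know the arm.

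If such patients leave the primary set, what remains is no longer the groups formed by randomisation. Difficult operations are likely to differ from the rest in node yield, which is the primary outcome, and the same selection would carry over to disease-free and overall survival. MITT would then exclude nearly everyone PP excludes, and their agreement would say little.

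**Working it through.** **1. Does the text remove these patients from the primary set?**

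| Rule | Known before allocation? | Could depend on arm? | Does the text say the patient stays in MITT? |
|---|---|---|---|
| Exclusion 15, conversion | No | Yes | No |
| Withdrawal 3, incomplete D2/R0 from nodal masses or vessel encasement | No | Partly: the anatomy predates surgery, the judgement does not | No |
| Withdrawal 4, additional surgery | No | Yes | No |
| Withdrawal 8, protocol violation | No | Yes | No |
| Missing data | No | Possibly | No |

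No sentence links these rules to MITT in either direction. The sample size gives a further indication.

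**2. The plan's own figure.** Inputs from Sample size: difference 3, SD 8.6, one-sided alpha 0.05, power 0.80. The two-sample t-test calculation with d = 3/8.6 gives 102.3 per group, rounded up to 103. Then 103/(1 − 0.20) = 128.75, rounded up to 129, and 4 × 129 = 516. The stated figures reproduce. The allowance is 129 − 103 = 26 per group, or 104 in total. The outcome is counted from the surgical specimen, so little of this can be late loss to follow-up.

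**3. Illustrative bias (assumed values; the documents give no removal rates by arm).** Let p be the share removed and k the node deficit of removed patients.

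- *Deficit measured from the whole-arm mean.* The retained mean exceeds the arm mean by k·p/(1 − p), so the bias in dual minus control is k[pD/(1 − pD) − pC/(1 − pC)]. With k = 6 and pC = 0.20:
  - pD = 0.15: 6 × (0.1765 − 0.25) = −0.44 nodes, 15% of the 3-node target.
  - pD = 0.10: 6 × (0.1111 − 0.25) = −0.83 nodes, 28% of the target.
- *Deficit measured from retained patients.* The bias is k(pD − pC): 6 × (−0.05) = −0.3 and 6 × (−0.10) = −0.6 nodes, 10–20% of the target.

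Both shifts go against the dual tracer, and both reverse sign if the two rates are exchanged.

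**4. Effect on error rates (also assumed).** Take 20% removed in one arm and 10% in the other, with removed patients 4.3, 8.6 or 12.9 nodes (0.5, 1 or 1.5 SD) below those retained. The absolute bias is 0.10 times the deficit: 0.43, 0.86 or 1.29 nodes. The standard error is 8.6 × √(1/103.2 + 1/116.1) = 1.16.

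- Tracer arm loses more: one-sided type I error is about 0.10, 0.18 or 0.30 instead of 0.05.
- Control loses more: power at 3 nodes is about 0.71, 0.58 or 0.43.
- Equal removal (20%) with equal deficits: no bias.
- Equal removal (20%) with deficits differing by 2, 4 or 6 nodes: bias 0.4, 0.8 or 1.2 nodes.

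**5. Power if patients are kept.** With SD 8.6 and no dilution of effect, one-sided power for 3 nodes is 80.5% with 103 per group and 87.6% with 129.

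**The case against.** The strongest defence is that the article does not define MITT, and set definitions are commonly left to the full protocol or SAP. Keeping MITT and PP as separate analyses suggests that they differ, so MITT may retain some of these patients. This stands as a limit: the effect on MITT is an inference, not something the text states. It does not dispose of the point, because the removal rules themselves are stated, conversion makes a patient ineligible outright, and nothing shown reverses that.

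Three stronger readings are tempting and not supported:

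- *Morbidity would be reported as near zero.* The complications criterion is limited to inability to tolerate surgery or anaesthesia. Data analysis sets up a separate safety population for adverse events, Postoperative parameters grades complications, and Adverse event reporting covers every death within 30 days of the last treatment day. No text drops these events from safety reporting.
- *Incomplete video withdraws the patient.* The rule disqualifies the procedure. It does not say that the patient leaves the study or the analysis.
- *Any incomplete dissection leads to withdrawal.* Criterion 3 is confined to nodal masses or vessel encasement, which is largely anatomy present before surgery. Unblinded judgement can still enter, but the criterion is narrower than a general completeness test.

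The 20% allowance may also cover voluntary withdrawal and missing data, so it indicates removal around surgery without proving it.

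**Conclusion.** The point holds in limited form. An intraoperative event is listed as an eligibility exclusion, several withdrawal criteria arise only after open allocation, and the text does not keep the affected patients in the primary set. Following it as written exposes the primary node comparison to post-randomisation selection and leaves MITT close to PP.

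The size and direction of bias cannot be derived from the documents. Under the assumed rates and a 6-node deficit, the shift is 0.3–0.83 nodes (10–28% of the 3-node target), against the dual tracer if control loses more and in its favour if the dual arm loses more. If removal is equal in rate and in kind across arms, there is no bias. The fault is in the primary analysis and cheap to correct, so it should be corrected before analysis.

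**What to change.** - Delete conversion from the eligibility exclusions and keep it as a recorded outcome.
- Define the primary (MITT) set as all randomised patients who undergo gastrectomy, in their allocated arm, regardless of conversion, D2/R0 completeness, complications or protocol deviations.
- Use the withdrawal criteria only to define PP.
- State that incomplete photographs or video do not remove a patient from MITT, and that a missing item does not withdraw a participant whose node count is known.
- Keep these patients in the safety population and in survival follow-up. State how disease-free survival is handled for patients without R0 resection, who have no clear disease-free starting point.
- Report removals by arm and reason, including randomised patients who had no gastrectomy.

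The cost is amendment wording, follow-up of the patients now retained, and a slightly more variable node count. The planned 516 suffice.

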### Outcome

The primary outcome is the total number of retrieved LNs. The secondary outcomes include positive rate, false positive rate, negative rate, false negative rate, number of metastatic LNs, rate of LN metastasis, relationship between LN metastasis and dual staining, morbidity and mortality, 3-year disease-free survival rate, 3-year overall survival rate, 3-year recurrence rate, postoperative recovery, duration of surgery, changes in body weight, intraoperative blood loss, intraoperative mortality, incision length, body temperature, and changes in lab parameters (albumin, prealbumin, hemoglobin, white blood cells, C-reactive protein, etc.).

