#### Follow-up records

Before discharge, various forms of health education such as dietary brochure and popular science lecture are provided to each participant to clarify the importance of regular follow-up visits. For patient who fails to visit on time for reexamination, telephone contact will be carried out to advise prompt reexamination. All participants will be followed-up every 3 months for the first 2 years and every 6 months since the third year (i.e., 1, 3, 6, 9, 12, 15, 18, 21, 24, 30, and 36 months) after discharge. Table 1 will be filled out at each visit. Tumor recurrence or metastasis and survival status of all participants will be assessed accordingly.

**Table 1 Tab1:** Follow-up sheet for each participant

Time point since surgery (month)	1	3	6	9	12	15	18	21	24	30	36
Actual date	√	√	√	√	√	√	√	√	√	√	√
Physical examination	√	√	√	√	√	√	√	√	√	√	√
Blood routine	√	√	√	√	√	√	√	√	√	√	√
Blood biochemistry	√	√	√	√	√	√	√	√	√	√	√
Tumor related indicators	√	√	√	√	√	√	√	√	√	√	√
Chest plain scan	√	√	√	√	√	√	√	√	√	√	√
Upper gastrointestinal endoscopy					√				√		√
Abdominal CT			√		√		√		√	√	√
Abdominal ultrasound	√	√				√		√			

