### Date management

Electronic CRFs will be stored in a standardized database with periodical backups, and paper CRFs will be submitted to the trial office. Prior to enrollment, clinical investigators and statistical analysts will receive uniform training in data entry, date extraction, and data analysis. The study database will be exposed only to trial staffs who have been trained and authorized. Data analysts will extract data from CRFs and review data for accuracy and completeness. For participants with missing data, missing values will not be supplemented, and the participants will be withdrawn from the study.

Identity and privacy of the participants will be strictly protected. Each enrolled participant will be assigned a subject ID number after signing the informed consent form. This unique ID number will represent the subject’s identity and be entered into the database. Data collected from subject will be stored under the ID number. Several measures will be taken to minimize the disclosure of subjects’ personal information, including (1) only authorized investigators can link the trial data chain of subjects to the subjects themselves through the identification form maintained by the study site, and (2) regulators and supervision departments of this study will conduct on-site review on the original data and strictly keep confidential. Data collection, transfer, processing, and storage will comply with data protection and privacy regulations throughout the study.

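### Withdrawal item (7) and the missing-data rule conflict with assessing recurrence and survival in all participants, so secondary 3-year outcomes may go uncollected in patients who stop

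*Protocol article*

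**What the plan says.** Three sections of the protocol article bear on this.

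- **Withdrawal criteria, item (7):** "voluntary withdrawal or discontinued treatment due to personal reasons at any stage". Voluntary withdrawal and stopping treatment share one item, with no time limit and no statement of what is still collected afterwards.
- **Date management:** for participants with missing data, "missing values will not be supplemented, and the participants will be withdrawn from the study".
- **Follow-up records:** visits are set at "1, 3, 6, 9, 12, 15, 18, 21, 24, 30, and 36 months", and "Tumor recurrence or metastasis and survival status of all participants will be assessed accordingly". For a missed visit the stated measure is that "telephone contact will be carried out to advise prompt reexamination".

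The Outcome section lists "3-year disease-free survival rate, 3-year overall survival rate, 3-year recurrence rate" among the secondary outcomes. On the primary endpoint it says: "The primary outcome is the total number of retrieved LNs".

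**The concern.** Stopping treatment and leaving the study are different events. The study intervention is a single operation, with or without tracer. Once it is done, the allocated treatment has been delivered, and a patient who later gives up care for personal reasons can still contribute recurrence and survival data. Item (7) gives that patient the same label as one who refuses further participation. The missing-data rule adds a second route out, because a gap in the data can itself lead to withdrawal.

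Both rules pull against the commitment to assess everyone. If site staff follow the withdrawal rules, status after the stopping date may never be recorded, and no later analysis can recover it. The 3-year outcomes would then rest on those who kept attending, whose prognosis may differ.

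**Working it through.** **1. The rules applied to three patients**

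| Patient | Withdrawal criteria and Date management | Follow-up records |
|---|---|---|
| A: operated as allocated, later stops care for personal reasons | Withdrawn under item (7), if stopping treatment covers later care | Still a participant whose status is to be assessed |
| B: only misses visits | Not covered by item (7); withdrawn under the missing-data rule if the gap remains | Telephoned and advised to return; status to be assessed |
| C: withdraws voluntarily | Withdrawn under item (7) | Included if the commitment to all participants is read literally |

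A and C cannot be told apart under item (7). For A and B the sections give different answers.

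**2. The plan's only figure on loss**

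The Sample size section allows 20% dropout: 103 / 0.8 = 128.75, rounded up to 129 per group, and 4 × 129 = 516. This reproduces. The allowance is 129 − 103 = 26 per group, or 104 in all. It belongs to the lymph node calculation and is not divided into early and late loss, so it does not say how many will stop during follow-up.

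**3. Possible size for OS**

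The protocol gives no event rates and no prognosis for patients who stop. Every input here is therefore an assumption:

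- 3-year OS of 75% in attenders, with exponential survival: λ = −ln(0.75)/36 = 0.00799 per month, S(t) = exp(−λt).
- A fraction p = 10% or 20% stop at a time uniform between months 1 and 36.
- Their hazard is h = 2 or 3 times higher from the start.

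True OS = (1 − p) × 0.75 + p × 0.75^h. For p = 20%, h = 3: 0.8 × 0.75 + 0.2 × 0.4219 = 0.684.

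If stoppers are censored when they stop, Kaplan-Meier tends to exp(−∫ λ[(1 − p)S + h·p·S^h·G] / [(1 − p)S + p·S^h·G] dt) over 0 to 36 months. G(t) is the probability of not yet having stopped: 1 before month 1, then (36 − t)/35.

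| p | h | True OS | Censored estimate | Difference (points) |
|---|---|---|---|---|
| 10% | 2 | 73.1% | 74.0% | +0.8 |
| 10% | 3 | 71.7% | 73.1% | +1.4 |
| 20% | 2 | 71.3% | 72.9% | +1.6 |
| 20% | 3 | 68.4% | 71.1% | +2.7 |

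Simulation of the same model agrees to within 0.1 point. With h = 1 both columns are 75.0% and there is no bias.

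**4. If stoppers are deleted instead**

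Those removed are the patients alive at their stopping time; a patient who died earlier was observed to die. OS in those kept = (1 − p) × 0.75 / [(1 − p) + p(1 − E)], where E is the average of S^h over the stopping times: 0.754 for h = 2 and 0.661 for h = 3.

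- p = 10%: 73.0% (h = 2) and 72.3% (h = 3), differences −0.1 and +0.6 points.
- p = 20%: 70.7% (h = 2) and 69.1% (h = 3), differences −0.6 and +0.7 points.

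The sign varies. With h = 1, E = 0.865 and deletion gives 73.9% (p = 10%) or 72.6% (p = 20%) against a true 75.0%, which is too low by 1.1 or 2.4 points. The no-bias statement therefore applies to censoring only.

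**The case against.** The best defence is that Follow-up records commits the trial to status for every participant, and no section says that collection stops on withdrawal. That stands. A reader might infer that recurrence and vital status are certain to be lost; the text shows a conflict between sections, not a settled end to follow-up.

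Other parts of the defence also stand:

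- **The call.** Its stated purpose is to bring the patient back, but this does not exclude asking about status. Call content is detail that an article may leave to the full protocol or case report form, so its absence is not an error here.
- **The reading of item (7).** The six items before it concern the surgical or perioperative period, so its treatment clause may have been meant that way too. Its own wording carries no such limit.
- **Prognosis.** A reader might infer that those who stop are the likeliest to have relapsed or died. This is plausible, but the document does not show it.
- **A larger bias.** A reader might compare 75% in attenders with the true 68-73% and claim a 2 to 7 point overestimate if stoppers are dropped. That also deletes patients who died under observation before they stopped. Removing only those alive at stopping gives −0.6 to +0.7 points in the four scenarios, so a general claim that survival is overestimated fails.
- **A false difference between arms.** This needs stopping to differ by arm. Participants know their allocation, so it could, but the follow-up schedule is the same in all arms and the document points to no such imbalance.

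The defence does not remove the conflict. Item (7) and the missing-data rule are stated rules, not omitted detail, and their wording can be used to end follow-up.

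**Conclusion.** The point holds as a conflict between sections that should be reconciled. Item (7) merges stopping treatment with leaving the study, Date management withdraws participants with missing data, and neither fits the commitment to assess everyone. Recurrence and vital status may go uncollected in patients who stop.

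Only the secondary 3-year disease-free survival, OS and recurrence outcomes are affected. The lymph node count is fixed at surgery and pathology, and the sample size rests on it alone. For OS the illustrative size is about 1 to 3 points too high under censoring, on the assumed inputs, and nil if stopping is unrelated to prognosis. Disease-free survival and recurrence were not quantified. This is a change that should be made, not one on which the primary result depends.

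**What to change.** 1. Split item (7). Under (a), the participant stops treatment or visits but stays in the study, and recurrence and survival status are collected to month 36. Under (b), the participant withdraws consent to data collection; this alone ends collection, and data up to that date are kept.
2. Align Date management so that a missing value does not by itself remove a participant from follow-up.
3. On the call already planned for missed visits, and at month 36 for anyone not seen, record vital status, date and cause of death, date last known alive, and recurrence (yes or no, date, site).

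The cost is a change of wording in the protocol and consent form and a few fields on an existing call. No clinical management changes. Recurrence reported by telephone is less precise than imaging and should be flagged in the data; vital status does not have this weakness.
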